Acupuncture is an easy-to-use, low-cost adjunct to traditional SLT to enhance language outcomes in individuals with PSA. It is one of the main treatments of traditional Chinese medicine (TCM) and has been used for thousands of years. During the past decade, the results of several meta-analyses have concluded that acupuncture after stroke seems to be effective in improving PSA functional communication and language function [17, 18]; however, most of the studies did not assess therapeutic effects over extended periods. For acupuncture treatment, long-term efficacy is considered one of the most important therapeutic effects, which has been suggested by numerous clinical studies [19–25]. It represents the cumulative effect of positive achievements [16]. Long-term efficacy will allow the patient's therapeutic effects to accumulate (“more is better”). Our previous studies on the effects of acupuncture on PSA have shown that participants in the acupuncture group had lower severity than the control group in week 4, but the difference was not significant; however, a significant reduction in PSA severity during weeks 5 to 12 was noted [26]. In addition, we explored the traditional Chinese medical theory and acupuncture technique of this acupuncture programme [27, 28]. Acupuncture has also been shown to have long-term efficacy in chronic pain and tinnitus, which has shown effective therapeutic results [29, 30]. Therefore, we speculate that the long-term therapeutic effect for PSA will also be well maintained; however, the long-term efficacy of acupuncture compared with the placebo effect in patients with PSA has not been investigated.

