### 2.6. Sample Size Calculation

No large RCTs have been carried out within the field examining the long-term effects of acupuncture on PSA. Previous studies have used interventions not applicable to the current protocol and have been of varying quality and used small sample sizes. We were, therefore, unable to calculate the prior accurate sample size. Thus, our RCT will support a more accurate sample size estimate and inform a definitive trial examining the long-term effectiveness of acupuncture for aphasia. The study involves the experimental study of functional magnetic resonance imaging (fMRI) and EEG for language tasks, which falls under the scope of experimental psychology. Taking into account individual psychological differences, it is expected that the PSA patients to be included will be divided into 2 groups. The number of patients to be included in the statistics in each group will be 20. Considering a drop-out rate of 20%, the target recruitment number is 48 participants (24 per group).

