### 2.9. Statistical Analysis

#### 2.9.1. Clinical Data Analysis

All statistical analyses will be performed by a statistician from the Clinical Evaluation and Analysis Centre of Dongzhimen Hospital affiliated to BUCM using Statistical Package for the Social Sciences (SPSS) V.22.0. The statistician will be blinded to the allocation of groups. The level of significance is established at *α* < 0.05 with a two-tailed test. The main objective is to compare the change in the AQ score at week 12 from baseline between the acupoint group and the NA control group. The null hypothesis is that the acupoint group will show the same change as the NA control group, while the alternative hypothesis is that the acupoint group shows a greater improvement. Categorical data will be represented by percentages, whereas continuous data will be represented by the average, standard deviation, median, minimum value, and maximum value. For comparison with the baseline, a *t*-test or nonparametric test will be used for continuous data and nonparametric tests for categorical data. For comparison of two independent samples, if the residuals are normally distributed, the analysis of covariance (ANCOVA) will be used for the primary outcome and subgroup analysis stratified by aphasia severity, *t*-tests for other continuous data, and chi-square tests for categorical data; if the residuals are non-normally distributed, a nonparametric test will be used for both the continuous and categorical data. The results of the intention-to-treat (ITT) analysis will be used to assess the validity of the study as a whole. The ITT analysis will collect data from all the participants in this trial, and for those lost to follow-up, the last observation carried forward method will be implemented.

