## 3. Discussion

PSA has proven to be difficult to treat. There is a degree of spontaneous recovery in the subacute phase, so there are few studies on the subacute phase of PSA. However, the subacute phase also requires treatment. The extant literature shows that acupuncture is probably effective for PSA [18, 45–47]. We intend to evaluate the long-term efficacy of acupuncture in maintaining speech production function. One common problem is the lack of standardization of acupoint selection, needle retention time, number of needles used, needling depth, and needle manipulation in acupuncture research.

From 2006 to now, we attempted to explore the general acupuncture scheme based on syndrome differentiation. In our PSA acupuncture treatment programme, DU20 is located in the area at the top of the head and is particularly closely related to the regulation of brain speech activity. The EX-HN1 are the acupuncture points around the DU20, both of which are used together to benefit the brain and promote speech rehabilitation. The treatment of PSA by EX-HN12 and EX-HN13 bloodletting has a theoretical basis in TCM and unique clinical efficacy. CV23 is mainly used for the treatment of speechlessness, stabbing into the skin towards the root of the tongue, and has the effect of restoring speech. The acupuncture theory of HT5 and GB39 to be used in our study is different from the traditional meaning of these points. FMRI can help us evaluate the changes of needle-related neuroplasticity, so we have conducted fMRI experiments based on this pair of effective points for aphasia. Electroacupuncture at HT5 and GB39 may modulate language and cognition function through a complex network formed by an extensive area of the brain cortex. It is beneficial to the recovery of language function [47]. In previous studies, we have demonstrated that this acupuncture protocol has shown significant improvements in auditory comprehension, reading, and dictation in patients with subacute PSA after 4 weeks of treatment. Therefore, we would like to know more about whether this treatment programme has long-term effects in these areas and observe the association with overall linguistic changes.

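### LOCF is the only stated rule for patients lost to follow-up: it shrinks a late-emerging effect on week-12 AQ and, if loss differs between arms, biases the primary comparison

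*Protocol article*

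**What the plan says.** The main objective (Section 2.9.1) is to "compare the change in the AQ score at week 12 from baseline between the acupoint group and the NA control group", at a level of "< 0.05 with a two-tailed test". If residuals are normal, "the analysis of covariance (ANCOVA) will be used for the primary outcome and subgroup analysis stratified by aphasia severity"; otherwise a nonparametric test is used. On the analysis set: "The results of the intention-to-treat (ITT) analysis will be used to assess the validity of the study as a whole". All participants are kept in, and "for those lost to follow-up, the last observation carried forward method will be implemented". This is the only missing-data rule in the article.

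The Abstract and Table 1 place the language assessments at baseline and weeks 4, 12 and 24. Section 2.6 plans 20 analysed patients per group, allows for 20% dropout and recruits 24 per group. It does not say when the losses are expected or how they split between arms.

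Two statements bear on whether a carried-forward value is reasonable. Section 3 says: "There is a degree of spontaneous recovery in the subacute phase". Section 1 reports from the group's earlier study that "participants in the acupuncture group had lower severity than the control group in week 4, but the difference was not significant", followed by a significant reduction in severity over weeks 5 to 12.

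**The concern.** Only a baseline or week-4 AQ can be carried to week 12. LOCF therefore assumes that language stopped changing when the patient left, either at zero change or at a value about eight weeks old. That sits badly with the article's own account. Patients enter 1 to 6 months after stroke, both arms receive speech and language therapy, some recovery is expected regardless of arm, and the earlier benefit was clearest after week 4.

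Two things are at stake. First, a real late effect is diluted. Section 2.6 says the trial is meant to inform the size of a definitive one. An effect understated by 20% would raise that trial's sample size by a factor of 1/0.8² = 1.56 at the same SD. Second, if one arm loses more patients, or loses them earlier, it is credited with less natural recovery. The arms can then differ at week 12 even if acupuncture does nothing.

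**Working it through.** **The plan's own figure.** 20 × 1.20 = 24 per group, 48 in total, as stated. (20/0.80 would give 25 per group and 50 in total; the gap of two patients does not matter here.) Twenty per cent of 24 is 4.8, about five patients per arm. Section 2.6 gives no effect size, SD or power, so the inputs below are assumptions.

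**Assumed inputs.** True week-12 difference e12 = 8 AQ points, or 0 under the null. Week-4 difference e4 as shown. Natural gain g in each interval (baseline to week 4, week 4 to week 12) of 2, 5 or 8 points. Dropout unrelated to outcome. p is the fraction lost before week 12, and s the share of those lost before week 4.

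Two simulation set-ups were used, each with 24 per arm, ANCOVA and a two-sided 5% test. Set-up A has AQ SD 15 and visit correlations 0.75 to 0.85. Set-up B has SD of change 7 at week 4 and 10 at week 12, correlation 0.7 and g = 8, with 6,000 trials per scenario (Monte Carlo error about 0.3 percentage points on a 5% rate). Observed-case means ANCOVA on patients with a week-12 value.

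**Step 1: attenuation with equal dropout.** Expected LOCF difference = (1 − p)·e12 + p·(1 − s)·e4. When e4 = 0 the timing share s drops out.

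| p | s | e4 | Expected LOCF difference | Shrinkage | Power, LOCF vs observed-case |
|---|---|---|---|---|---|
| 0.20 | any | 0 | 0.8×8 = 6.4 | 20% | 52% vs 66% (A); 47% vs 66% (B) |
| 0.20 | 0.5 | 2 | 6.4 + 0.2×0.5×2 = 6.6 | 17.5% | 49% vs 65% (B) |
| 0.20 | 0 | 4 | 6.4 + 0.2×4 = 7.2 | 10% | 66% vs 66% (A) |
| 0.10 | any | 0 | 0.9×8 = 7.2 | 10% | 64% vs 72% (A) |
| 0.10 | 0 | 4 | 7.2 + 0.1×4 = 7.6 | 5% | 71% vs 72% (A) |

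Set-up B gave mean LOCF estimates of 6.41 and 6.61 for the first two rows, agreeing with the hand calculation.

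**Step 2: bias with no true effect.** With pA and pC the fractions lost in the acupoint and control arms, the bias (acupoint minus control) is (pC − pA)·[2g − (1 − s)·g]. For s = 0.5 this is (pC − pA)·1.5g; for s = 0 it is (pC − pA)·g. The sign is against the arm that loses more, whichever that is.

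| Dropout by arm | g | s | Size of bias | Type I error, LOCF |
|---|---|---|---|---|
| 20%/20% | 8 | 0.5 | 0 | 4.9% (B); 4.7% in A |
| 20%/20% | 8 | 0 | 0 | 5.4% (B) |
| 15%/25% | 5 | 0.5 | 0.10×7.5 = 0.75 | 6.0% (A) |
| 15%/25% | 8 | 0.5 | 0.10×12 = 1.2 | 7.1% (B) |
| 15%/25% | 8 | 0 | 0.10×8 = 0.8 | 5.5% (B) |
| 10%/30% | 2 | 0.5 | 0.20×3 = 0.6 | 5.9% (A) |
| 10%/30% | 5 | 0.5 | 0.20×7.5 = 1.5 | 8.3% (A) |
| 10%/30% | 8 | 0.5 | 0.20×12 = 2.4 | 11.7% (A); 12.5 to 12.9% (B) |
| 10%/30% | 8 | 0 | 0.20×8 = 1.6 | 7.6 to 8.7% (B) |

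Where B shows a range, it depends on which arm loses more. With 10%/30% dropout, no recovery after week 4 and all losses after week 4, the bias is zero and type I error is 4.8% (B). Observed-case ANCOVA stayed between 4.5% and 5.6% in every null scenario of set-up B.

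**Step 3: timing alone.** With 20% lost in each arm and g = 8, suppose one arm loses all of them before week 4 and the other all between weeks 4 and 12. The shortfalls are 0.20×16 = 3.2 and 0.20×8 = 1.6, a bias of 1.6 points against the arm with the earlier losses.

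**Step 4: a true effect with unequal dropout (B, e12 = 8, e4 = 0, s = 0.5).** Acupoint 30%, control 10%: 0.7×8 − 2.4 = 3.2 (simulated 3.19, power 15%). Acupoint 10%, control 30%: 0.9×8 + 2.4 = 9.6 (simulated 9.63, power 82%). The error can run either way.

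**The case against.** A reader might infer that the primary result is biased and its error rate lost in all circumstances. The documents do not support that. With equal dropout unrelated to outcome, type I error stays near 5% and LOCF is conservative. Inflation needs loss that differs between arms, and the article predicts no such difference. Participants are blinded, and the arms share visits, session schedule and speech therapy. The 10%/30% split is a chosen scenario. This stands, but it gives no assurance either: the procedures differ (bloodletting and manipulation for de qi in the acupoint arm only), Table 1 tracks discomfort and acceptance of acupuncture, and nothing in the plan secures equal loss.

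A reader might also infer that the effect is expected only after week 4. That is too strong. Section 1 says severity was already lower at week 4, though not significantly, and Section 3 reports improvement in some language domains after four weeks of treatment. Some early effect is plausible, and it reduces the attenuation.

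Nor can the whole 20% be placed before week 12. Section 2.6 does not date it, follow-up runs to week 24, and losses after week 12 leave the primary endpoint untouched. The 20% shrinkage is therefore an upper figure if dropout matches the plan.

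The amount of natural recovery is unknown too. Section 1 says these patients rarely recover spontaneously, which pulls against Section 3, and entry extends to six months after onset. With little recovery the bias is small. Finally, the trial is presented as informing a definitive one, and sensitivity analyses are often left to an analysis plan. That argues for a lower severity, but the primary handling rule itself is fixed in the article.

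**Conclusion.** The point holds in conditional form, as a should-fix. The only stated rule for losses on the primary endpoint conflicts with the article's own description of recovery.

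- **Attenuation:** up to about 20% if all planned dropout precedes week 12 and there is no week-4 effect. It is about 5 to 10% if only half of it does, or if losses come after week 4 and half the effect is already present then.
- **Bias and type I error when loss differs between arms:** about 6 to 7% at 15%/25%, and about 6 to 13% at 10%/30%, for recovery of 2 to 8 AQ points per interval with half the losses before week 4. Later losses give smaller figures.
- **Equal dropout unrelated to outcome:** type I error near 5%.

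The mechanism follows from the visit schedule and the rule. The sizes rest on an assumed AQ SD, gains, correlations, effect and dropout timing, none of which the article gives. The valid comparator simulated was observed-case ANCOVA with dropout unrelated to outcome; the mixed model suggested below was not itself simulated.

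**What to change.** In Section 2.9.1, replace LOCF as the primary handling with an analysis that is valid under missing at random and uses all observed AQ values. Either of these would do:

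- a mixed model for repeated measures with baseline AQ, visit, group and group × visit, taking the week-12 contrast as the primary test; or
- multiple imputation followed by the planned ANCOVA.

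Add one delta-adjusted or reference-based sensitivity analysis, since missing at random cannot be verified. Keep LOCF, if at all, only as a labelled sensitivity analysis.

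The cost is a change of wording and a little analysis time. AQ is already scheduled at all four visits, so no new data are needed.

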#### 2.9.2. MRI Data Analysis

For imaging, data will be analyzed using the Data Processing & Analysis for (Resting-State) Brain Imaging (DPABI) toolbox [44] performed on MATLAB V.8.6 (MathWorks) to detect any changes in brain function due to acupuncture treatment. Lesion symptom mapping was demarcated on T1-weighted images manually using MRIcroGL (http://www.cabiatl.com/mricrogl/) in native space by neurologists who were blinded to the participants' language scores. DTI images will be analyzed using MATLAB (https://www.mathworks.com/) and FMRIB Software Library (http://www.fmrib.ox.ac.uk/fsl). After data preprocessing, some data-driven approaches will be performed to investigate neuroplasticity between the two groups, such as the amplitude of the low-frequency fluctuation, regional homogeneity, and voxel-wise degree centrality. A two-sample *t*-test will be conducted to investigate the differences in brain regions between the acupoint group or NA control group in the DPABI software. Multiple comparisons will be used to better control for a highly inflated false positivity rate. Pearson's correlation analysis will be performed to examine the association between the fMRI data and clinical variables.

#### 2.9.3. EEG Data Analysis

EEG data will be preprocessed by NeuroScan software, and electrocardiogram, ophthalmic, and myoelectric artefacts will be removed by independent component analysis (ICA). eLORETA software will be used to extract the characteristic indexes of the brain network. The electric current sources in different brain regions will be accurately and intuitively calculated, and the functional network characteristics of the brain in different frequency bands will be analyzed.

#### 2.9.4. ERP Data Analysis

Using the threshold selection method based on a small-world network across different thresholds to build a functional brain network, analyses will be conducted to examine the network topological structure of the brain under the different thresholds, build different threshold brain networks, and use the theory of the complex network diagram analysis method to calculate the weighted aggregation coefficient, weighted characteristic path length, and small-world network features.

## 3. Discussion

PSA has proven to be difficult to treat. There is a degree of spontaneous recovery in the subacute phase, so there are few studies on the subacute phase of PSA. However, the subacute phase also requires treatment. The extant literature shows that acupuncture is probably effective for PSA [18, 45–47]. We intend to evaluate the long-term efficacy of acupuncture in maintaining speech production function. One common problem is the lack of standardization of acupoint selection, needle retention time, number of needles used, needling depth, and needle manipulation in acupuncture research.

From 2006 to now, we attempted to explore the general acupuncture scheme based on syndrome differentiation. In our PSA acupuncture treatment programme, DU20 is located in the area at the top of the head and is particularly closely related to the regulation of brain speech activity. The EX-HN1 are the acupuncture points around the DU20, both of which are used together to benefit the brain and promote speech rehabilitation. The treatment of PSA by EX-HN12 and EX-HN13 bloodletting has a theoretical basis in TCM and unique clinical efficacy. CV23 is mainly used for the treatment of speechlessness, stabbing into the skin towards the root of the tongue, and has the effect of restoring speech. The acupuncture theory of HT5 and GB39 to be used in our study is different from the traditional meaning of these points. FMRI can help us evaluate the changes of needle-related neuroplasticity, so we have conducted fMRI experiments based on this pair of effective points for aphasia. Electroacupuncture at HT5 and GB39 may modulate language and cognition function through a complex network formed by an extensive area of the brain cortex. It is beneficial to the recovery of language function [47]. In previous studies, we have demonstrated that this acupuncture protocol has shown significant improvements in auditory comprehension, reading, and dictation in patients with subacute PSA after 4 weeks of treatment. Therefore, we would like to know more about whether this treatment programme has long-term effects in these areas and observe the association with overall linguistic changes.

Regarding the study design, we developed an assessor- and participant-blinded design to minimize bias. The specific effects are thought to be generated by needling the acupoint with the appropriate manipulation. The nonspecific effects are due to other aspects of the therapy, such as the expectations of the patient, which might influence the treatment outcome. To recognize the specific effects, a placebo is needed. Among acupuncture research, placebo controls for acupuncture studies have been difficult to select. To maximally exclude the placebo effect, rigorous methodological designs are followed. In our study, control conditions involve being punctured with real acupuncture needles at NA locations. Thus, the self-perception of placebo effects in the NA control group is difficult to distinguish from the real acupoints. Additional needle manipulations will not be used in the NA control group. De qi is a characteristic constellation of sensations felt by patients during acupuncture needling. It has been regarded as an important factor related to clinical effects; however, we do not pursue this kind of sensation in the NA control group. By following these methods, participants can be successfully blinded, and the efficacy of acupuncture could be confirmed if the results of the acupoint group prove superior to those of the NA control group.

We will assess patients with PSA on multiple levels, including multiple neuropsychological tests, functional and structural brain alterations, and TCM syndrome evaluation. This multidomain assessment will be used to identify possible biomarkers involved in the effects of acupuncture in PSA.

It is worth mentioning that functional and structural brain alterations will be used as outcome measures. MRI allows for noninvasive evaluations of neural functional changes [48]. fMRI studies use two modalities, task-related and resting-state methods [49]. Task-related fMRI has revealed functional disturbances in individuals with aphasia. MRI may be more sensitive to smaller treatment effects. It can be used as a tool to assess the efficacy of acupuncture in treating aphasia. These analyses may identify whether neural efficiency is improved or the brain connectome is reorganized to achieve language enhancement. Electrophysiological methods, such as intracranially recorded EEG or ERP, are particularly promising to offer a mechanistic understanding of language formation processes. Compared with the language scales alone, the combination of in vivo measures of brain alterations in this study will be more sensitive in detecting acupuncture efficacy [50].

Therefore, this study can provide clinical evidence on the long-term efficacy of our acupuncture programme in patients with PSA and explore biomarkers for the recovery of function and the efficacy of acupuncture in patients with PSA through a multidimensional evaluation. This trial will fill the gaps in the evidence on the long-term efficacy of acupuncture for aphasia and provide a model for the multimodal evaluation of PSA.

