In terms of the current state of evaluation of aphasia, the requirements for a comprehensive evaluation of PSA have not yet been fully implemented. One of the important means was to evaluate the language characteristics of PSA, which is the major part of the evaluation; however, to date, this single evaluation approach is often insufficient. As such, neuropsychological tests in conjunction with in vivo measures may be more sensitive than neuropsychological tests alone in the assessment of brain structure and electrophysiology [31–33]. We introduce MRI and EEG for evaluation of the objective characteristics of PSA because the multimodal assessment of brain structure and function allows for a more objective evaluation of the recovery characteristics of patients with aphasia. Based on the previous study [34], we conducted a TCM syndrome evaluation of PSA patients and confirmed the relationship between linguistic features and TCM syndrome. Therefore, in this study, we have also introduced the evaluation of TCM syndrome to provide more comprehensive evidence of efficacy based on the combined evaluation of Chinese and Western medicine. For the reasons above, we propose to investigate whether acupuncture treatment on PSA has the value of maintaining long-term efficacy through this randomized controlled trial (RCT) with multimodal evaluation.

We designed an assessor- and participant-blinded RCT with PSA patients. Using NA acupuncture as a control, the trial aims to identify the efficacy of acupuncture by answering two questions: (1) what is the long-term efficacy and reliability of acupuncture as an intervention for PSA compared with the placebo effect? and (2) what interactions will be observed through an integrated evaluation of linguistic features, brain function, and TCM syndrome?

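### The Discussion says brain measures will make this study more sensitive to efficacy, but no stated analysis supports that, and the imaging comparison between arms is a t-test with no baseline covariate

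*Protocol article*

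**What the plan says.** Section 3 (Discussion) compares the planned assessment with language scales alone and states that "the combination of in vivo measures of brain alterations in this study will be more sensitive in detecting acupuncture efficacy". The statement is about this study and carries no qualification. The same idea appears twice in weaker form: earlier in the Discussion, "MRI may be more sensitive to smaller treatment effects", and in the Introduction, "neuropsychological tests in conjunction with in vivo measures may be more sensitive than neuropsychological tests alone".

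The analyses are set out separately by modality:

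- **AQ (2.9.1).** "The level of significance is established at *α* < 0.05 with a two-tailed test". If residuals are normal, "the analysis of covariance (ANCOVA) will be used for the primary outcome and subgroup analysis stratified by aphasia severity".
- **MRI (2.9.2).** A two-sample t-test "will be conducted to investigate the differences in brain regions between the acupoint group or NA control group". On multiplicity: "Multiple comparisons will be used to better control for a highly inflated false positivity rate". The indices listed include a voxel-wise one. A Pearson correlation links fMRI data with clinical variables.
- **EEG and ERP (2.9.3, 2.9.4).** Network features are derived; these sections describe no joint analysis with the language scales.

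On numbers, 2.6 says "The number of patients to be included in the statistics in each group will be 20", with 48 to be recruited. It adds that an accurate sample size could not be calculated.

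**The concern.** The sentence credits the design with a property that has to come from its tests, and the tests described do not supply it. A correlation between fMRI and clinical variables does not test the treatment effect, and nothing else joins the two kinds of data.

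Taken one at a time, the imaging comparisons start with two handicaps relative to the AQ. They face a stricter threshold because of the multiplicity control. They are also specified as a plain two-sample t-test, while the AQ gets covariance adjustment. The second handicap is avoidable, because every patient is to be scanned at baseline.

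What is at stake is interpretation and precision, not the primary result. A reader who accepts the sentence could take an empty map as evidence against efficacy, or let a positive map outweigh a null AQ result. Meanwhile the imaging comparison gives up precision that the baseline scan could provide.

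**Working it through.** **1. The plan's own figure.** 20 per arm with 20% dropout is given as 24 per arm, 48 in total. 20 × 1.2 = 24 reproduces this; 20 / 0.8 = 25 per arm would be the usual inflation. The difference is two patients in total and does not matter here. The plan gives no power, detectable difference or sensitivity figure, so there is nothing further to reproduce.

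**2. Inputs.** From the article: n = 20 analysed per arm (2.6), 1:1 allocation (2.2), two-sided 0.05 for the AQ (2.9.1). Assumed: 80% power; imaging thresholds of 0.01, 0.001 and 0.000001 (the last is 0.05 / 50,000, Bonferroni over 50,000 voxels); correlation r between baseline and follow-up of 0.5 or 0.7; baseline value as the ANCOVA covariate. Differences are in SD units of the follow-up value.

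**3. Two-sample t-test.** Power is the probability that a noncentral t with 38 degrees of freedom and noncentrality d × √(n/2) = 3.162 d exceeds the two-sided critical value. Solving for 80%:

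| Threshold | Critical t | Detectable d | Ratio to 0.91 |
|---|---|---|---|
| 0.05 (AQ, unadjusted) | 2.02 | 0.91 | 1.00 |
| 0.01 | 2.71 | 1.13 | 1.24 |
| 0.001 | 3.57 | 1.41 | 1.55 |
| 0.000001 | 5.82 | 2.15 | 2.36 |

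Check on the first row by the normal approximation: (1.960 + 0.842) × √(2/20) = 0.89.

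**4. Effect of baseline adjustment.** ANCOVA multiplies the detectable difference by √(1 − r²) and uses one degree of freedom (37 remain). The factor is 0.866 at r = 0.5 and 0.714 at r = 0.7.

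- AQ at 0.05: 0.91 × 0.866 = 0.79 SD; 0.91 × 0.714 = 0.65 SD.
- Imaging at 0.001: 1.41 × 0.866 = 1.22 SD; 1.41 × 0.714 = 1.01 SD.

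**5. If change scores are compared.** Section 2.7.1 says that changes in activation and connectivity will be compared between groups, so the t-test may be meant for change from baseline. The factor is then √(2(1 − r)). At r = 0.5 it is 1.00, so the change-score t-test also needs 1.41 SD and ANCOVA's gain is unchanged. At r = 0.7 it is 0.775, giving 1.09 SD against 1.01 SD by ANCOVA. Above r = 0.5 the gain is therefore smaller than step 4 suggests.

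**6. Power for a true difference of 0.8 SD in both measures.**

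| | AQ at 0.05 | Imaging at 0.001 |
|---|---|---|
| Both unadjusted | 69% | 17% |
| Both adjusted, r = 0.7 | 93% | 50% |
| AQ adjusted (r = 0.7), imaging not | 93% | 17% |

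The last row mixes two causes. The first two rows isolate the threshold; going from 17% to 50% in the imaging column is what the baseline covariate adds.

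**The case against.** The strongest reply is that the sentence concerns adding brain measures to language scales, not replacing them. The AQ keeps its full 0.05, so secondary imaging cannot make the whole assessment less sensitive than the scales alone. That stands, and the figures above do not contradict it.

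A reader might go further and infer that imaging needs a far larger effect than the AQ and will usually miss one that the AQ finds. The article does not support this. It names no correction method, threshold, or number of voxels or regions, and no SD or effect size. Cluster-level or false-discovery-rate control would change the ratios. A stricter threshold means lower sensitivity only if the standardised brain effect is less than about 1.2 to 2.4 times the AQ effect, and nothing in the article bears on that. Setting 93% beside 17% is also uneven, because only the AQ is given baseline adjustment.

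It is also fair that the AQ is already the primary outcome and MRI and EEG are secondary, used for neuroplasticity, and that no section says a negative map would count against efficacy. The misreading is a risk that the sentence invites, not a stated rule. The unnamed threshold and the absence of EEG and ERP arm comparisons from their sections are details that an article may leave to a fuller document, and they are not held against the plan.

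What remains is the unqualified claim, the absence of any joint test behind it, and an imaging test stated without a baseline covariate.

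**Conclusion.** The claim of greater sensitivity is unsupported by the analyses and sample size described; it is not shown to be false. At 20 per arm and 80% power, the stated imaging t-test detects 1.13 to 2.15 SD over the assumed thresholds, against 0.91 SD for the unadjusted AQ. Only the direction is firm: at equal n and equal adjustment, any threshold stricter than 0.05 needs a larger standardised difference. The size of the gap rests on the assumed thresholds, and its consequence on an unknown brain effect.

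The part worth changing in the analysis is the missing baseline covariate. At 0.001 it is worth a fall from 1.41 to 1.22 SD (r = 0.5) or 1.01 SD (r = 0.7), or from 1.09 to 1.01 SD at r = 0.7 if change scores were intended. The AQ analysis is unaffected.

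**What to change.** 1. In 2.9.2, replace the two-sample t-test with a comparison of arms on each imaging index at week 12, with the baseline scan value of that index as covariate, keeping the multiplicity control. The baseline scan is already scheduled, so the cost is one degree of freedom and a usable scan at both times for each patient analysed.
2. In the Discussion, change the claim from will to may, in line with the Introduction. Add that efficacy is judged on the AQ and that a non-significant map is not evidence of no effect. This costs wording only. To keep the stronger claim, the authors would have to specify a joint analysis of brain and language measures that tests the treatment effect.
3. Optional: name a short list of regions before unblinding, correct across that list only, and treat the remaining maps as exploratory. This eases the threshold but gives up some of the data-driven search that 2.9.2 sets out to do, so it is the authors' choice.
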